# A multicenter, randomized controlled trial of immediate total-body CT scanning in trauma patients (REACT-2)

**DOI:** 10.1186/1471-227X-12-4

**Published:** 2012-03-30

## Abstract

**Background:**

Computed tomography (CT) scanning has become essential in the early diagnostic phase of trauma care because of its high diagnostic accuracy. The introduction of multi-slice CT scanners and infrastructural improvements made total-body CT scanning technically feasible and its usage is currently becoming common practice in several trauma centers. However, literature provides limited evidence whether immediate total-body CT leads to better clinical outcome then conventional radiographic imaging supplemented with selective CT scanning in trauma patients. The aim of the REACT-2 trial is to determine the value of immediate total-body CT scanning in trauma patients.

**Methods/design:**

The REACT-2 trial is an international, multicenter randomized clinical trial. All participating trauma centers have a multi-slice CT scanner located in the trauma room or at the Emergency Department (ED). All adult, non-pregnant, severely injured trauma patients according to predefined criteria will be included. Patients in whom direct scanning will hamper necessary cardiopulmonary resuscitation or who require an immediate operation because of imminent death (both as judged by the trauma team leader) are excluded. Randomization will be computer assisted. The intervention group will receive a contrast-enhanced total-body CT scan (head to pelvis) during the primary survey. The control group will be evaluated according to local conventional trauma imaging protocols (based on ATLS guidelines) supplemented with selective CT scanning. Primary outcome will be in-hospital mortality. Secondary outcomes are differences in mortality and morbidity during the first year post trauma, several trauma work-up time intervals, radiation exposure, general health and quality of life at 6 and 12 months post trauma and cost-effectiveness.

**Discussion:**

The REACT-2 trial is a multicenter randomized clinical trial that will provide evidence on the value of immediate total-body CT scanning during the primary survey of severely injured trauma patients. If immediate total-body CT scanning is found to be the best imaging strategy in severely injured trauma patients it could replace conventional imaging supplemented with CT in this specific group.

**Trial Registration:**

ClinicalTrials.gov: (NCT01523626).

## Background

Injuries are the cause of 5.8 million deaths annually which accounts for almost 10% of global mortality [1]. Among adults aged 15-59 years the proportion of injuries as cause of death is even higher, ranging from 22% to 29% [1]. Injuries, whether unintentional or intentional, may have devastating effects on the lives of individuals and poses a great burden on public-health budgets [2]. This burden may even increase in the future, since the World Health Organization (WHO) projected a 28% increase in global deaths due to injury between 2004 and 2030 [1].

Specialized trauma centers all over the world provide initial trauma care and diagnostic work-up of trauma patients. This work-up is standardized and frequently based on the Advanced Trauma Life Support (ATLS^®^) guidelines which include a fast and priority-based physical examination as well as screening radiographs supplemented with selective Computed Tomography (CT) [3]. ATLS guidelines advise to routinely perform X-rays of thorax and pelvis and Focused Assessment with Sonography for Tauma (FAST) in trauma patients. X-rays of the spine and extremities are performed based on clinical suspicion during the secondary survey. Whether or not to perform CT scanning following conventional imaging is defined less clearly in the ATLS guidelines and depends upon national guidelines and local protocols.

In recent years CT has become faster, more detailed and more available in the acute trauma care setting. CT shows high accuracy for a wide range of injuries [4-7] which is reflected by a low missed diagnosis rate [5,8-10]. Hence, the conventional radiological work-up according to the ATLS may not be the optimal choice of primary diagnostics anymore. Furthermore, severely injured patients frequently require secondary CT scanning of many parts of the body after conventional imaging. Modern multi-detector CT scanners (MDCT) can perform imaging of the head, cervical spine, chest, abdomen and pelvis in a single examination (total-body CT scanning). The past few years this total-body imaging concept gained popularity as a possible alternative to the conventional imaging strategy. With the use of immediate total-body CT scanning in trauma patients, rapid and detailed information of organ and tissue injury becomes available and a well-founded plan for further therapy can be made.

In the past, CT scanners were located in the radiology department, frequently even on another floor than the emergency department (ED) where the trauma patient is admitted. The past assumption that total-body CT scanning in severely injured trauma patients is too time consuming may no longer be held, since an increasing number of trauma centers have a CT scanner available at the ED or even in the trauma room itself [11,12]. Several studies evaluated time intervals associated with total-body CT usage in severely injured patients [4,5,8,13-18]. Time intervals focused on are scanning time, time to all diagnosis known and time in the ED. Some studies compare different scanning protocols [19-21], some evaluate the effects of a total-body CT scan in one group trauma patients [5,8,9], while others make a comparison in two cohorts trauma patients, one evaluated with an immediate total-body CT scan and one evaluated with ATLS based imaging protocols and selective CT scanning [22-25]. Although these studies are incomparable with respect to design, CT scanners used, diagnostic work-up protocols and trauma populations[26], the main conclusion is clear. Total-body CT scanning in trauma patients is not as time consuming as was once expected and may even be time saving compared to conventional imaging protocols supplemented with selective CT.

The most important question remains whether immediate total-body CT scanning will translate to improved clinical outcome. A recent study in 4621 trauma patients reported a significant increase in the probability of survival for patient given immediate total-body CT scanning compared with conventional imaging strategies supplemented with selective CT scanning [25]. However, since the study was retrospective in nature, no correction for all confounding variables could have been made. Patients who underwent immediate total-body CT scanning were on average more severely injured than those who did not receive total-body CT scanning. Differences between participating centers and protocols used for diagnostic work-up were not described. Whether the positive effect in survival in patients who underwent total-body CT scanning can be attributed solely to the total-body CT scan itself remains therefore unclear.

Although literature provides limited evidence for the usage of an immediate total-body CT scan in the work-up of trauma patients, more and more trauma centers encourage and are implementing immediate total-body CT scanning in the diagnostic phase of primary trauma care. Since the burden of total-body CT scanning in terms of costs and radiation dose is at least controversial [20,27,28], the advantage of performing an immediate total-body CT scan should be proven in high quality studies resulting in high level evidence in order to make its implementation justifiable.

In order to assess the value of immediate total-body CT scanning in severely injured trauma patients, the Academic Medical Center (AMC) in Amsterdam, the Netherlands, has initiated an international multicenter randomized controlled trial. Severely injured patients, who are thought to benefit the most from a total-body imaging concept, will be included. Such a trial has never been done before and is crucial to provide evidence whether or not the usage of immediate total-body CT scanning in the diagnostic phase of primary trauma care is justifiable.

## Methods/design

### Study objectives

The primary objective is to determine the effects of immediate total-body CT scanning during the primary trauma survey on clinical outcomes compared to patients who are evaluated with standard conventional Advanced Trauma Life Support (ATLS^®^) based radiological imaging. The secondary objectives are to assess the effects of total-body CT scanning on long term clinical outcomes, quality of life, clinically relevant time intervals in the early phase of trauma care and the differences in treatment strategies used.

### Study design

The REACT-2 trial is an international, multicenter randomized clinical trial in six high-volume trauma centers that will compare the effects of immediate total-body CT scanning in severely injured trauma patients with conventional imaging protocols.

### Setting

In total four trauma centers in The Netherlands, one Swiss and one American trauma center will participate in the REACT-2 trial. All participating hospitals are level-1 trauma centers with a multi-slice CT scanner located in the trauma resuscitation room or at the ED.

When a patient arrives in the trauma room a brief report of the pre-hospital circumstances, medical assessment and clinically suspected injuries is presented to the trauma team leader by the ambulance personnel. The initial evaluation of trauma patients will be done according to the ATLS guidelines for the primary survey. Potential life-saving interventions during the primary survey and before any imaging include securing the airway by intubation or performing a cricothyrotomy, chest tube insertion, pericardiocenthesis or taking hemorrhage controlling measurements such as applying a pelvic binder or external pressure on bleeding sites to (temporarily) stabilize the vital functions. Usually, peripheral intravenous access is taken care of by the ambulance personnel, but if not, at least one intravenous catheter will be inserted before radiologic imaging takes place. Based on information received from the ambulance personnel and the findings during primary survey, the trauma team leader decides on the eligibility of the patient to participate in the trial. If the patient is found to be eligible randomization takes place. Figure 1 depicts the study flow chart.

**Figure 1 F1:**
[figure not shown]
**Study flow chart REACT-2 trial**.

The intervention group will receive a total-body CT scan from head to pelvis. In the intervention group conventional radiography of the torso and FAST will be completely omitted. The CT protocol for the consists of a two-step whole-body acquisition (from vertex to pubic symphysis) starting with Head and Neck Non Enhanced CT (NECT) with arms alongside the body. The preferred technique for the second complementary scan is a split-bolus intravenous contrast directly after repositioning of the arms alongside the head, and this second scan covers thorax, abdomen and pelvis. Participating centers however are free to choose their own technique as long as intravenous contrast is given for the chest and abdominal part of the total-body CT.

The control group will be evaluated according to a conventional trauma protocol with selective CT scanning. The REACT-2 trial has been designed to maximize the applicability of the trial's results to usual care settings. Therefore, the technical details of the CT scanning done in the control group are not specified and participating centres follow their own protocols. Indications for the selective CT scanning however are pre-defined based on the combined local protocols of the participating centers. These standardized protocols provide a basis for the comparison of the two imaging approaches.

### Study population

All non-pregnant trauma patients aged 18 years and older having life-threatening (respiratory, circulatory or neurologically) conditions with compromising vital parameters, with clinical suspicion on specific injuries or with specific injury mechanisms are included. Patients in whom the scanning will hamper necessary (cardiopulmonary) resuscitation or who require an immediate operation because of imminent death (both as judged by the trauma team leader) are excluded. Detailed in- and exclusion criteria are summarized below:

### Inclusion criteria

Trauma patients with the presence of life-threatening vital problems defined as at least one of the following:

- respiratory rate ≥ 30 min of ≤ 10/min;

- pulse ≥ 120/min;

- systolic blood pressure ≤ 100 mmHg;

- estimated exterior blood loss ≥ 500 ml;

- Glasgow Coma Score ≤ 13;

- Abnormal pupillary reaction onsite.

OR

Patients with one of the following clinically suspicious diagnoses:

- flail chest, open chest or multiple rib fractures;

- severe abdominal injury;

- pelvic fracture;

- unstable vertebral fractures/spinal cord compression;

- fractures from at least two long bones.

OR

Patients with one of the following injury mechanisms:

- fall from height (> 3 m/> 10 ft);

- ejection from the vehicle;

- death occupant in same vehicle;

- severely injured patient in same vehicle;

- wedged or trapped chest/abdomen.

### Exclusion criteria

Trauma patients with one of the following characteristics will be excluded:

- known age < 18 years;

- known pregnancy;

- referred from another hospital;

- clearly low-energy trauma with blunt injury mechanism;

- penetrating injury in 1 body region (except gun shot wounds) as the clearly isolated injury;

- any patient who is judged to be too unstable to undergo a CT scan and requires (cardiopulmonary) resuscitation or immediate operation because death is imminent according to the trauma team leader in mutual agreement with the other leading care givers.

### Endpoints

The primary outcome criterion for this trial is in-hospital mortality.

As secondary parameters for the trial focus on additional clinical consequences for the patients and cost-effectiveness and cost-utility:

- mortality (24-h, 30-day and 1-year mortality);

- morbidity (complications and total number of (re-)interventions and re-admissions up to 6 months post trauma; transfusion requirements, length of ICU stay and number of ventilation days);

- several time intervals during initial evaluation (time of arrival, time to CT, scanning time, time to diagnosis and time in the ED);

- radiation exposure;

- quality of life 6 and 12 months after the trauma as recorded by completing the EuroQol-6D;

- general health 6 and 12 months after the trauma as recorded by completing the HUI-3;

Economic parameters/endpoints:

- total costs of imaging during the initial/index hospital stay;

- total direct and indirect medical and non-medical costs during the first half year posttrauma;

- quality adjusted life-years (QALY's).

### Randomization

If a patient is eligible for the trial the diagnostic imaging pathway for initial assessment in the trauma resuscitation room will be determined by randomization. The randomization will be performed immediately after inclusion at computers located in the trauma room of the participating hospitals. Randomization will be performed using a 'one-click' computer program on a 1:1 basis per hospital with varying block sizes of 2, 4, 6, 8, 10 and 12. The trauma team will be directly informed on the outcome of the randomization so that imaging can be started. A standardized case record from (CRF) will be used. This CRF is totally web-based via a secured internet module.

### Sample size calculation and data analysis

A previous study reported a reduction in mortality from 15% to 8.6% with total-body CT scanning as the single diagnostic procedure during trauma evaluation as compared to historical control data [29]. Analysis on the large German polytrauma registration database performed by Huber-Wagner et al. showed a significant reduction in the 24-h mortality in patient who underwent immediate total-body CT compared to the conventional group (10% vs. 12%, P = 0.038) [25]. Historical AMC data show a mortality rate of 12% for trauma patients matching the current trial inclusion criteria. Based on the combination of the AMC data and the participation of the other trauma centers with comparable trauma populations, it is expected to find a reduction in mortality from 12% to 7%. The detection of such a difference requires 539 patients per group using a power of 80% and a two-sided alpha of 5%. Based on the historical and estimated data of the participating centers the inclusion period will take about 1,5 years and the follow-up period will take an additional year.

The main analyses of primary and secondary outcomes will be conducted for all randomized patients according to the result of the randomization (intention-to-treat). Data are expressed as percentages for categorical data, as mean and standard deviation (SD) for normally distributed numerical data and as median, range, and, where appropriate, inter-quartile range (IQR = 25 to 75%) for non-normally distributed numerical data.

The following subgroups will be used for subgroup analysis:

- multitrauma patients (defined as Injury Severity Score (ISS) >/=16);

- severe traumatic brain injury patients (defined as admission Glasgow Coma; Scale (GCS) ≤ 8 and an Abbreviated Injury Score (AIS)-head of ≥ 3);

- penetrating versus blunt trauma.

A p-value less than 0.05 is considered statistically significant. If appropriate, predictive values between variables are calculated. Predictive values in continuous outcome variables are assessed using a multivariate regression model, and binary outcome measures are assessed using a multivariate logistic regression model. In case of binary outcome measures, predictive values are expressed as Odds Ratio's (OR) with 95% Confidence Intervals (CI). Data are analyzed using the Statistical Package for the Social Sciences (SPSS) version 18.0 SPSS Inc., Chicago, IL.

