## Discussion

The need for prospective studies to measure the effect of immediate total-body CT scanning in trauma care has been stressed recently by several authors [8,22,23,25,29]. Retrospective studies have shown the possible benefits in time and outcome of immediate total-body CT scanning in trauma patients. The next step is to compare its usage to the current best imaging strategy according to ATLS guidelines in a prospective trial.

The primary question that needs to be answered is whether immediate total-body CT scanning in severely injured trauma patients decreases mortality and significant morbidity when compared to conventional imaging strategies supplemented with CT. Therefore, randomization is within the hospital, ensuring that a comparison between imaging protocols is made per hospital instead of between hospitals. The design of the trial is multi-centered, with participating centers in The Netherlands, Switzerland and North America. This design assures that differences in trauma populations, trauma mechanisms and workflow in different parts of the world are taken into account as well. This is important to make sure that if an effect on outcome is seen that this can solely be attributed to the usage of a total-body CT scan.

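### Randomisation is stratified by hospital, but the stated analysis carries neither hospital nor any pre-randomisation predictor into the mortality comparison; a named adjusted primary model would be a cheap gain in power

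*Protocol article*

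**What the plan says.** All places are in the protocol article.

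- **Endpoints:** "The primary outcome criterion for this trial is in-hospital mortality".
- **Randomization:** allocation is made "on a 1:1 basis per hospital with varying block sizes of 2, 4, 6, 8, 10 and 12".
- **Discussion:** randomising inside each hospital is described as "ensuring that a comparison between imaging protocols is made per hospital instead of between hospitals".
- **Sample size calculation and data analysis:** the trial is sized for a fall in mortality from 12% to 7%, with 539 patients per group, 80% power and a two-sided 5% level. The main analyses are by intention to treat. Regression comes last, for predictive values and only where appropriate. There, "binary outcome measures are assessed using a multivariate logistic regression model", with odds ratios and 95% confidence intervals. No covariates are listed, hospital is not mentioned, and no test or model is named for the effect of arm on in-hospital death.
- **Inclusion criteria:** eligibility uses findings available before randomisation, for example "Glasgow Coma Score ≤ 13", along with respiratory rate, pulse, systolic pressure and pupillary reaction.

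**The concern.** The Randomization and Discussion sections rest on a within-hospital comparison, but the analysis section contains nothing that makes the comparison within hospital. The one multivariable model is pointed at a different purpose, prediction, and its use is optional. A reader cannot tell which model gives the primary result.

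Two things are at stake, of unequal weight:

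- **Consistency.** The stratification factor should appear in the primary analysis because the protocol says the comparison is per hospital.
- **Efficiency.** About 102 deaths are expected in the whole trial. Level of consciousness, age and vital signs are plausible strong predictors of death after trauma. A model that uses pre-randomisation predictors would get more power from the same patients.

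A multivariable model with unnamed covariates also leaves room for covariates that should not be used. ISS and AIS-head already appear in the subgroup definitions. Both depend on injuries found by imaging, and imaging is what differs between the arms.

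**Working it through.** **1. The plan's own figure.** Inputs from the sample size section: p1 = 0.12, p2 = 0.07, two-sided alpha 0.05, power 0.80. The mean proportion is 0.095. The pooled-variance formula without continuity correction is

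n = [1.960 × √(2 × 0.095 × 0.905) + 0.8416 × √(0.12 × 0.88 + 0.07 × 0.93)]² / 0.05²

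= (1.960 × 0.4147 + 0.8416 × 0.4132)² / 0.0025 = (0.8127 + 0.3477)² / 0.0025 = 538.7, so **539 per group**.

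This matches exactly, and power at 539 is 80.0%. Other conventions give 578 (continuity-corrected), 536 (unpooled) and 531 (arcsine). The design basis is therefore an unadjusted comparison of two proportions.

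**2. Expected deaths.** 539 × (0.12 + 0.07) = 102.

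**3. Simulation of adjustment.** There were 2,500 trials per scenario, each with 1,078 patients in six equal hospitals, randomised 1:1 within hospital, with marginal mortality set to 12% and 7%. Logistic Wald tests were run unadjusted, with hospital, and with hospital plus one baseline prognostic score. The document gives neither the between-hospital SD (logit scale) nor the AUC of baseline prognosis, so both are assumptions. The Monte Carlo standard error of each power is √(0.8 × 0.2 / 2500) = 0.8 points. The models were fitted to the same simulated trials.

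Hospital only, no prognostic score:

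| Hospital SD | Unadjusted | With hospital | Gain (points) |
|---|---|---|---|
| 0 | 80.4% | 80.9% | 0.5 |
| 0.3 | 79.6% | 80.1% | 0.5 |
| 0.6 | 82.2% | 82.8% | 0.6 |

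Hospital plus prognostic score, hospital SD 0.3:

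| Assumed AUC | Unadjusted | With hospital | With hospital and score | Total gain (points) |
|---|---|---|---|---|
| 0.70 | 80.2% | 80.8% | 83.0% | 2.8 |
| 0.79 | 79.7% | 80.2% | 86.2% | 6.5 |
| 0.88 | 80.8% | 81.3% | 91.7% | 10.9 |

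Nearly all the gain comes from prognosis, not from hospital.

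**4. The same gain in patients.** Putting powers of 83.0%, 86.2% and 91.7% into the formula of step 1 (z = 0.954, 1.089, 1.385) gives about 583, 638 and 768 per group for an unadjusted analysis. That is 44, 99 and 229 more per group than 539.

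**5. Validity of the test.** With 12% mortality in both arms, simulated type I error was 5.3 to 5.4% unadjusted and 5.3 to 5.8% adjusted. The standard error is √(0.05 × 0.95 / 2500) = 0.44 points, so the largest value lies about 1.9 standard errors above 5%.

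An analytic check gives the same message. Take assumed hospital mortalities of 5, 8, 10, 12, 16 and 21% (mean 12%). The mean within-hospital variance is 0.1028 and the pooled variance is 0.12 × 0.88 = 0.1056, a ratio of 0.974. The nominal 5% unadjusted test then has a true size of 2 × [1 − Φ(1.96/√0.974)] = 4.7%, which is slightly conservative.

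**6. Size of the model.** Arm, five hospital terms, GCS and age make 8 parameters, so 102 / 8 is about 13 deaths each. Adding systolic pressure and respiratory rate as one term each makes 10 parameters, about 10 deaths each.

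**The case against.** The strongest reply is that this is an article condensing a fuller protocol, and that covariate lists usually sit in an analysis plan that is not shown. A reader might infer that the trial rejects hospital and baseline variables, or commits itself to a crude pooled test. The text supports neither reading. No test is named for the primary comparison, and the multivariable model does not say what enters it. The accurate statement is that the document names neither hospital nor a predictor and does not link its model to the primary comparison.

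A reader might also infer that omitting hospital breaks the per-hospital claim or invalidates the test. It does not. Blocking within hospital balances the arms in each hospital, so hospital cannot materially confound even a pooled comparison. Type I error is not materially affected, and the sample size section itself expects comparable populations. Chance imbalance in GCS is likewise already allowed for in the error rate of a randomised test.

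Three further objections stand and limit the claim:

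- The power gain comes from a single, perfectly measured and correctly specified score, at AUCs that the document does not give. The model actually fitted will probably gain less.
- The data are not all shown to exist. Admission GCS is needed for a subgroup definition. The inclusion criteria list thresholds, which does not show that continuous vital signs are recorded for everyone. The exclusion criterion is worded as known age under 18, so age may be unknown at inclusion. The Setting section allows intubation before imaging, which can make GCS and respiratory rate uninformative.
- The complaint that the trial is sized on a risk difference but reports only an odds ratio is weak. Categorical data are to be given as percentages, and the economic evaluation counts extra patients alive.

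What the reply does not remove is that the article goes as far as model type, effect measure and software, yet directs its model at prediction and leaves the randomised comparison without one.

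**Conclusion.** The point holds as a worthwhile, low-cost improvement, not as an error that threatens the result. Following the text as written gives a valid test with the stated 80% power. Including hospital adds about 0.5 points; the reason to include it is agreement with the randomisation and with the Discussion. Including pre-randomisation prognosis could add roughly 3 to 11 points at the same sample size. That range rests on an assumed AUC of 0.70 to 0.88, an assumed between-hospital SD of 0.3 and an ideal risk score, so it should be read as an upper guide.

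**What to change.** State one primary analysis and fix it before anyone who chooses the model sees outcomes by arm:

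- **Model:** logistic regression of in-hospital death on arm, hospital, admission GCS and age, using values from before randomisation. Add systolic pressure and respiratory rate only if their values are captured. Enter respiratory rate as abnormal yes/no or non-linearly, because the inclusion criteria treat both extremes as abnormal.
- **Excluded covariates:** no adjustment for ISS or AIS-head.
- **Effect measures:** the standardised (marginal) risk difference with 95% CI beside the odds ratio.
- **Missing covariates:** one simple rule set in advance, covering at least GCS in intubated patients and unknown age.
- **Sensitivity analysis:** the hospital-stratified Mantel-Haenszel estimate.

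The cost is a wording change, and the core model needs no new data if GCS and age are recorded. There are two drawbacks. The adjusted odds ratio is conditional and does not estimate the same quantity as the crude one, which is why the marginal risk difference is reported. The missing-covariate rule also has to be written and applied. The sample size need not change.
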